### Phase 1: Diagnostic Accuracy and Predictive Capacity of Turning Measures

#### Participants

Phase 1 will include approximately 50 civilians with persistent symptoms from mTBI, 50 civilian healthy controls, and 40 active-duty SM healthy controls. Three non-military sites (OHSU, UU, CKRC) will test civilians. A fourth military site (FSH) will enroll and test 40 active-duty SM healthy controls across a range of military experience and ability levels.

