**Cognitive DT outcomes**		
Cognitive-task accuracy	Assesses the percentage of cognitive task responses that are correct in dual-task conditions	To compare whether cognitive performance when turning is impaired in people with mTBI
Number of correct responses per second	Assesses the overall number of correct responses, divided by the overall time in seconds	

* *These measures will involve assessment of both the mean and the variability (i.e., standard deviation)*.

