To determine whether healthy active-duty SMs perform turning tasks differently than healthy civilians, we will fit linear regression models for each turning outcome with main effects of group (active-duty SMs vs. civilians) and adjusted for age, body mass index, and other potential covariates. Inferences will be made using a significance level of 0.05 and a Holm-Bonferroni adjustment for multiple comparisons. If we find outcomes significantly differ between active-duty populations and control populations, we can conclude that population-specific normative values are needed. Given the large sample size of active-duty SMs and controls, we will then separate active-duty and civilian control groups for future analyses using those outcomes with significant differences between active-duty and civilian control participants. If we fail to find differences between active-duty and civilian control groups, it suggests performance does not vary by service status, and normative means, standard deviations, and minimum detectable changes will be calculated by combining data from all healthy control participants. We will also compare the distributions of performance using interval estimators to determine the extent to which the range of performance overlaps between active-duty SMs and civilians.

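### Norms for service-member and civilian controls are pooled whenever a low-powered test is non-significant, and service status cannot be separated from site

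*Protocol article*

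**What the plan says.** Under Participants (Phase 1), the article plans "50 civilian healthy controls, and 40 active-duty SM healthy controls". It places the two kinds of control at different sites: "A fourth military site (FSH) will enroll and test 40 active-duty SM healthy controls", while civilians are tested at the three non-military sites.

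Under Secondary Statistical Analyses, "we will fit linear regression models for each turning outcome with main effects of group (active-duty SMs vs. civilians"). These models also adjust for age, body mass index and possibly further terms. On error control the article states: "Inferences will be made using a significance level of 0.05 and a Holm-Bonferroni adjustment for multiple comparisons". Two consequences follow.

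- Where an outcome differs significantly, the conclusion drawn is that "we can conclude that population-specific normative values are needed". The controls are then split for those outcomes: "we will then separate active-duty and civilian control groups for future analyses using those outcomes with significant differences between active-duty and civilian control participants".
- Where it does not, the article's reading is: "If we fail to find differences between active-duty and civilian control groups, it suggests performance does not vary by service status". It then takes all healthy controls together to compute the norms (means and standard deviations) and the minimum detectable change.

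The same paragraph describes the control sample as large. It ends by promising interval estimators of how far the two distributions overlap. It gives no equivalence margin, no smallest relevant difference and no power for this comparison.

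**The concern.** A non-significant test is not evidence that two groups perform alike unless the test could have found a gap that matters. Here the pooling decision rests on non-significance alone. The Holm correction makes it easier to declare sameness the more outcomes are tested, which is the wrong direction for a pooling rule.

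The opposite conclusion has its own problem. Among controls, active-duty status and the military site are the same variable, so a difference in course set-up, testers or equipment at that site would look exactly like a population difference, or could hide one.

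The most direct consequence is for normative ranges: a merged range could be wrong for one population or both. There may be a second consequence for the AUCs, depending on who counts as a control in the ROC analyses. Those AUCs are one of the four criteria used to choose the recommended task and outcome.

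**Working it through.** **The article's own figure.** The only two-group power statement is in Sample Size: 90% power for mTBI against controls, 50 per group, two-tailed alpha 0.01, at 65% of g = 1.20. That is 0.65 × 1.20 = 0.78 SD. The noncentral t distribution gives 89.6%, so the figure reproduces. It concerns a different comparison and a larger effect; nothing equivalent is given for service members against civilians.

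**Number of tests (an assumption).** Table 1 lists four starred measures and two unstarred ones, and of the starred ones it says "These measures will involve assessment of both the mean and the variability (i.e., standard deviation"). That makes 4 × 2 + 2 = 10 outcomes per task and condition.
- Three tasks, dual-task only: 3 × 10 = 30 tests.
- Three tasks, both conditions: 3 × 2 × 10 = 60 tests.
- One measure over three tasks and two conditions: 3 × 2 = 6 tests.

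The article does not say which family is meant, so I show the range.

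**Power for a 0.5 SD gap (an assumption).** Two-sided, noncentral t, 88 degrees of freedom, noncentrality 0.5 × √(50 × 40 / 90) = 2.36, alpha = 0.05/m (the first Holm step), ignoring covariate adjustment:

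| Tests m | Alpha | Power | Real gap missed and pooled |
|---|---|---|---|
| 1 (unadjusted) | 0.05 | 64% | 36% |
| 6 | 0.0083 | 37% | 63% |
| 30 | 0.0017 | 20% | 80% |
| 60 | 0.0008 | 14% | 86% |

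The first step is Holm's strictest, so the full procedure was also simulated. With 30 or 60 tests, correlation 0 or 0.5, and one, half or all outcomes differing, average power per outcome was 14% to 24%. By the normal approximation, the gap detectable with 80% power is 0.59 SD unadjusted, 0.85 SD with 30 tests and 0.89 SD with 60.

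**Site and service status.** A design matrix for the 90 controls with an intercept, a service-status term and three site indicators has 5 columns and rank 4. The service effect cannot be estimated apart from the military-site effect, and adding site to the model would not change that.

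**AUC, only if service members enter the ROC controls.** Assume normal outcomes with equal SD, a civilian mTBI deficit of d, and service members better than civilian controls by 0.5 SD. Then pooled AUC = (50/90) × Φ(d/√2) + (40/90) × Φ((d + 0.5)/√2).
- d = 0: 0.556 × 0.500 + 0.444 × 0.638 = 0.56, against 0.50 with civilian controls only.
- d = 0.78: 0.556 × 0.709 + 0.444 × 0.817 = 0.76, against 0.71.

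With a 0.3 SD advantage the same formula gives 0.54 and 0.74.

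**A confidence-interval rule instead.** SE of the difference = √(1/50 + 1/40) = 0.212 SD, so the 90% interval has a half-width of about 0.35 SD. With a ±0.5 SD margin and a true difference of zero, the chance of pooling is about 2 × Φ(0.5/0.212 − 1.645) − 1 = 52%. With a true gap equal to the margin it is at most about 5%, against 36% to 86% under the present rule.

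**The case against.** Several points on the other side have force.

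- The article says only that non-significance suggests no variation, and it adds interval estimates of overlap, so readers would see some estimation. This stands as mitigation, but the pooling itself depends only on the test.
- Minimum detectable change is less exposed than it looks. The repeatability paragraph already computes it for civilian controls, military controls and civilian mTBI separately as well as combined, and it rests on within-subject error, which a shift in group means does not bias. I accept this; the point concerns normative means and standard deviations.
- The lowest power figures depend on an assumed gap and an assumed family size, and covariate adjustment could move them. I accept this too, and hence give the full range. Even the most favourable case, with no adjustment, misses a half-SD gap about one time in three.
- A reader might infer that service members will join the ROC controls for every non-significant outcome and inflate the AUCs. The article does not say so. What it names as pooled is normative means, standard deviations and minimum detectable changes; what it means by future analyses is ambiguous; and Sample Size powers the group comparison on 50 civilians per group, which points to a civilian-only contrast. On the other hand, neither Statistical Analysis nor the task-refinement section restricts the healthy controls to civilians. The AUC effect is therefore conditional.
- Nor does the article establish that service members perform better. It enrols them over a range of experience and ability and raises faster turning only as a possibility.

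**Conclusion.** The pooling rule is unsound as written, and so is the attribution of a significant difference to population. Under an assumed 0.5 SD gap, a real difference would be merged into common norms about 36% of the time without multiplicity adjustment and up to 86% with 60 tests. The aliasing of service status with site needs no assumption: it follows from where each group is enrolled.

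The consequence for AUCs holds only on one reading of the article. If service members enter the ROC controls for the non-significant outcomes and are 0.5 SD better, an AUC of 0.50 becomes 0.56 and one of 0.71 becomes 0.76, and the AUCs being ranked would rest on different control sets. The documents support calling the ROC control group unclear; they do not support saying that the AUCs will be inflated.

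This is a secondary analysis and the main group comparison is unaffected on its stated basis, so the point should be fixed but does not undermine the trial.

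**What to change.** Three changes of wording, before the data are analysed:

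1. State that every ROC and AUC analysis compares the 50 civilian mTBI participants with the 50 civilian controls, for all outcomes. This may already be the intention.
2. Pool normative means and standard deviations only if the 90% confidence interval for the service-member minus civilian difference lies inside a margin fixed in advance, for example ±0.5 control SD. Otherwise report separate norms.
3. Report any difference as due to population or site. The design cannot separate the two, and no model term will.

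No new data are needed. The cost is that at a 0.5 SD margin truly equal populations would be pooled only about 52% of the time, so more outcomes keep separate norms. The standard error of a normative mean is then 1/√50 = 0.14 SD for civilians and 1/√40 = 0.16 SD for service members, instead of 1/√90 = 0.11 SD when pooled. A wider margin pools more often (76% at 0.6 SD, 90% at 0.7 SD) but tolerates a larger true gap, so the sponsor should justify the margin on what difference in norms would matter.

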### Phase 2: Responsiveness to Rehabilitation

#### Participants

Phase 2 will include 40 active-duty SMs with persistent symptoms from mTBI who are referred for physical therapy because of their symptoms. Participants will be recruited from two military medical centers specializing in the rehabilitation of active-duty personnel after mTBI, the Evans Army Community Hospital (EACH) at Fort Carson, CO; and Madigan Army Medical Center (MAMC) at Joint Base Lewis-McChord, WA. Each site will recruit 20 participants for Phase 2. Participants will be tested before and after their rehabilitation; this study will have no influence or input on the rehabilitation prescribed or delivered to the participants.

#### Inclusion and Exclusion Criteria

All participants must be active-duty SMs who are referred to either the EACH or MAMC for physical therapy following mTBI. All other inclusion and exclusion criteria will be identical to those in Phase 1.

#### Assessment Procedures

Participants will complete two assessments: a baseline assessment prior to the first rehabilitation session and a postrehabilitation assessment after the physical therapist determines the participant has completed his/her rehabilitation course. At each assessment, patients will complete symptom inventories (NSI, DHI, QOLIBRI) and will be outfitted with inertial sensors. Participants will then complete the three turning tasks described in Phase I while wearing the sensors. One block will be performed, consisting of one 1MW, one mIAT, and one CCTC performed with no additional cognitive task, and one 1MW, one mIAT, and one CCTC performed while simultaneously performing a cognitively demanding task. At the postrehabilitation assessment, participants will complete the Patients' Global Impression of Change Scale (PGIC) (82). Participants' adherence to their rehabilitation program will be measured by their attendance at scheduled physical therapy visits.

#### Primary Outcome Measures—Responsiveness to Rehabilitation

To determine the responsiveness to rehabilitation, we will (1) determine the clinically important difference for objective turning outcomes and (2) compare the standardized response mean of each to rehabilitation to the minimum detectable change calculated in Phase I.

To determine the clinically important difference of turning outcomes, changes in objective turning outcomes will be anchored to the PGIC. Linear regression models will be fit to determine the differences in objective turning outcomes that are associated with a unit improvement in the patients' activity, symptoms, emotions, and overall quality of life, based on the PGIC.

To compare the effect of rehabilitation to the minimum detectable change, calculated from Phase 1, for each outcome, we will compute the mean difference between pre-rehabilitation and post-rehabilitation for each objective turning outcome. For each outcome, the ratio of the mean difference over minimum detectable change will be calculated. Ratios >1 will indicate that the mean difference due to rehabilitation was greater than normal variation between measurements, with larger ratios indicating larger effects due to rehabilitation.

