#### Statistical Analysis

To evaluate the capability of objective, DT turning measures to discriminate between healthy controls and people with mTBI, we will construct receiver operating characteristic (ROC) curves using each objective turning outcome and clinical assessment of activity. The area under the ROC curve (AUC) will be calculated, and AUC confidence intervals will be generated through a bootstrapping procedure. We will compare the AUCs and confidence intervals between each objective turning measure and clinical assessment of activity using tests of equality and a 0.05 significance level with Holm-Bonferroni corrections to adjust for multiple comparisons.

To assess the capacity of DT turning measures to predict performance in civilian or military-relevant tasks, we will use Pearson correlation coefficients and linear regression models. Pearson correlation coefficients will compare the linear relationship between objective turning outcomes and the primary outcome of task completion time during the CAT and throughput during the SUP tasks within participants with mTBI, healthy control participants, and all participants together. To determine how changes in objective turning measures correspond to changes in functional performance, linear regression models will be built for each objective turning measure that was significantly associated with functional performance. The primary outcomes for the civilian and military-relevant tasks will be modeled as the dependent variable. To account for potential differences in performance between civilians and active-duty SMs, a group effect will be included as a covariate. Beta coefficients will be interpreted to identify the relative change in objective turning measures that are associated with changes equal in magnitude to 1 standard deviation of the healthy control participants' performance.

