### Refinement of Tasks and Outcomes for Future Clinical Use

To reduce the number of tasks and outcomes, a variable selection procedure will be implemented. First, objective turning outcomes for each task will be ranked according to their (1) AUC in differentiating people with mTBI from healthy control subjects, (2) correlation with functional performance in the civilian-relevant task, (3) correlation with functional performance in the military-relevant task, and (4) ratio of mean effect of rehabilitation over minimum detectable change. Outcome–task combinations will then be ordered according to the sum of their ranks across these four categories, where a lower total is better. The outcome, and associated task, with the lowest total sum will be identified and put forward in future applications and clinical training tools. Additionally, a civilian-specific task/outcome combination will be identified by summing the ranks, but excluding the rank corresponding to the correlation with functional performance in the military-relevant task. A military-specific task/outcome combination will be identified similarly, but summing all ranks except the correlation with functional performance during the civilian-specific task.

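### The Phase 2 clinically important difference is a regression value per PGIC unit, with no condition that turning change is related to the PGIC, so it has no meaning for a poorly anchored outcome

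*Protocol article*

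**What the plan says.** The responsiveness section of Phase 2 lists two determinations. The first is to "determine the clinically important difference for objective turning outcomes". The method is stated: "changes in objective turning outcomes will be anchored to the PGIC", and then "Linear regression models will be fit to determine the differences in objective turning outcomes that are associated with a unit improvement" in several patient-reported areas, from activity to overall quality of life, "based on the PGIC". The estimator, the increment (one unit) and the anchor are therefore fixed. The dependent variable is not named. No minimum correlation is given, and nothing is said about a null or wrong-signed slope.

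The anchor is collected once: "At the postrehabilitation assessment, participants will complete the Patients' Global Impression of Change Scale (PGIC"). The sample is small: "Phase 2 will include 40 active-duty SMs with persistent symptoms from mTBI".

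Two other places bear on the point. In the Phase 1 Statistical Analysis section, "linear regression models will be built for each objective turning measure that was significantly associated with functional performance", so an association condition is used there. In the section on refining tasks and outcomes, the responsiveness criterion is the "ratio of mean effect of rehabilitation over minimum detectable change"; the clinically important difference is not among the ranking criteria.

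**The concern.** An anchor gives a clinically important difference its meaning only if change in the measure follows the anchor. A regression returns a number per PGIC unit whether or not it does. As written, every turning outcome receives a value, including outcomes whose change has little to do with how patients judge their improvement. On the natural reading those outcomes receive the smallest values, which looks like a low bar for important change when it is really an absence of evidence.

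Some weak links are plausible. The anchor covers several areas of life and not turning alone. Table 1 lists six turning outcomes, four of them analysed as both mean and standard deviation, over three tasks and two conditions: (4 × 2 + 2) × 3 × 2 = 60 combinations. At stake is the credibility of the first of the two Phase 2 determinations. The Discussion foresees use of the results in rehabilitation and return-to-duty decisions.

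**Working it through.** The article gives no Phase 2 figure for power, anchor correlation or clinically important difference, so there is nothing to reproduce.

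**Inputs.** n = 40 (Phase 2 Participants). The correlation r between turning change and PGIC, and both standard deviations, are not given. Assumptions: r from 0 to 0.7, and SD(PGIC) of 1.0 or 1.5 units. Results are in SDs of turning change.

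**Turning change regressed on PGIC (natural reading).** Value per unit = r × SD(change)/SD(PGIC).

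| r | SD(PGIC) = 1.0 | SD(PGIC) = 1.5 |
|---|---|---|
| 0.7 | 0.70 | 0.47 |
| 0.5 | 0.50 | 0.33 |
| 0.3 | 0.30 | 0.20 |
| 0.1 | 0.10 | 0.07 |
| 0 | 0 | 0 |

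**PGIC regressed on turning change, then inverted.** Value per unit = SD(change)/(r × SD(PGIC)). With SD(PGIC) = 1.0 this is 1.43 at r = 0.7, 2.0 at 0.5, 3.3 at 0.3 and 10 at 0.1. The two versions differ by a factor of 1/r²: 4 at r = 0.5 (2.0/0.50) and 100 at r = 0.1 (10/0.10). The unnamed dependent variable therefore matters a good deal.

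**Sampling error at n = 40.** The standard error of the standardised slope is √((1 − r²)/(n − 2)). At r = 0.1 it is √(0.99/38) = 0.161, so the slope is only 0.1/0.161 = 0.62 standard errors from zero. Simulation with 20,000 samples per r gave a zero or negative slope in about 27% of samples at r = 0.1 and 10% at r = 0.2.

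**What a correlation condition can do at n = 40.** By Fisher's z, the 95% CI for an observed r of 0.3 is tanh(0.310 ± 1.96/√37), about −0.01 to 0.56. A two-sided 0.05 test of the anchor correlation has power of about 9% at r = 0.1, 47% at 0.3 and 92% at 0.5. A point-estimate cut-off of 0.3 would be missed about half the time by an outcome whose true r is 0.3. A correlation condition is therefore useful but imprecise, and the interval must be reported beside it.

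**The case against.** **Direction.** Because the dependent variable is not named, one cannot say flatly that a weaker link gives a smaller difference. The closest parallel, the Phase 1 functional-performance regression, has turning as the predictor; that form, inverted, inflates the value. This stands. It changes the direction of the distortion but not the conclusion, since neither version means anything for an unrelated outcome.

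**Detail left to an analysis plan.** A minimum anchor correlation and a responder category could sit in a document that is not shown. This is fair for details. But the article itself fixes the rule of one unit, by linear regression, for turning outcomes generally. Followed as stated, it yields a near-zero or wrong-signed difference for an unrelated outcome. The article also saw fit to state an association condition for Phase 1.

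**Impact.** A reader might infer that clinicians will classify noise as recovery, or that the wrong task will be selected. The article supports neither. It nowhere uses the clinically important difference to classify patients, the ranking does not include it, and the minimum detectable change is estimated separately in Phase 1. This stands and limits the harm.

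**Evidence of a weak link.** Nothing in the article shows that the correlation will be low. The contrast between r = 0.1 and r = 0.5 illustrates the formula and does not forecast this trial.

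**Scale and timing.** A single rating after treatment is inherent in a global impression of change. The article does not describe the scale steps, so whether they are equally spaced cannot be judged from it.

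**Conclusion.** The point holds in a limited form. The stated rule produces a clinically important difference for every turning outcome with no condition that the outcome is related to the anchor. If turning change is the dependent variable, the value is proportional to r: 0.07 to 0.10 SD of turning change at r = 0.1, 0.33 to 0.50 SD at r = 0.5, and 0 at r = 0, for an assumed PGIC SD of 1.0 to 1.5. If the model is reversed and inverted, a weak link gives an inflated value instead. The proportionality is algebra; the sizes rest on the assumed SD and r. With 40 participants a wrong-signed or zero slope is a real prospect for weakly anchored outcomes, at about 27% when r = 0.1. The effect is confined to the reported clinically important differences and does not reach the selection of tasks and outcomes. It should be settled before analysis.

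**What to change.** 1. State that turning change is the dependent variable.
2. For every outcome, report the correlation of turning change with PGIC and its 95% CI.
3. Report a clinically important difference, with its 95% CI, only for outcomes that reach a pre-set minimum correlation in the expected direction. A value of 0.3 would serve as an example; it is a convention, and imprecise at n = 40. For the rest, state that none can be derived.
4. Flag any value below the Phase 1 minimum detectable change as not usable for individual patients.

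Naming the PGIC level that counts as an important improvement would clarify the target, but it cannot replace step 3. In the same linear model the predicted change between two levels k units apart is k × slope, so it is still proportional to r and still zero at r = 0.

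The cost is wording only: the data are already planned and participants carry no extra burden. The downside is that some outcomes will have no clinically important difference, and a few well-anchored ones may miss the cut-off by chance. Reporting every correlation with its interval keeps that visible.
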